## 6 STATISTICAL CONSIDERATIONS

### 6.1 METHOD OF RANDOMISATION

Randomisation will be performed centrally at the MRC Clinical Trials Unit at UCL using a computer-implemented algorithm. The method of randomisation will be minimisation over a number of clinically important stratification factors with an allocation probability of 80%. Each comparison will have an independent randomisation programme.

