### 6.3.2 RADICALS-RT SAMPLE SIZE

In the patients suitable for this randomisation, the control arm is assumed to be deferred radiotherapy i.e. radiotherapy at PSA relapse.

When the trial was originally designed, there was uncertainty about the likely event rate but it was anticipated that a modest absolute effect in the order of 5% would be required to convince clinicians to adopt adjuvant radiotherapy for all patients. The original sample size calculations anticipated that around 2,600 patients would need to be recruited over 5½ years and followed-up for a further 7 years in order to obtain 80% power to detect an improvement from 70% to 75% or 90% power to detect an improvement from 80% to 85%.

From SWOG 8794 and EORTC 22911, the proportion of patients free of distant metastases at 10 years is estimated to be 90%. We would look to test whether adjuvant RT can improve this to 95% (hazard ratio 0.487), which is seen as the minimum clinically significant improvement required to routinely introduce adjuvant RT to this patient population; this mirrors the size effect observed in SWOG 8794. This is tested using the superiority design. With 80% power, a two-sided 5% significance level, accrual lasting 5½ years (reaching peak accrual rates after 3 years) and a further 7 years of follow-up, we would need to recruit 1,063 patients in order to observe 66 distant metastases events. This sample size assumes that 30% of patients are lost to follow-up and around 30 patients per month randomised from 30 months onward. Therefore, the target sample size will be reduced from 2,600 to around 1,063 patients. This assumes that 30% of patients are lost to follow-up between 5 and 10 years.

If the peak accrual is lower, at around 25 patients per month, accrual would be extended by 1 year, to around 6½ years and around 1,160 patients would be randomised; this should address the question with the same power and in the same overall timescale.

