### 6.3.3 RADICALS-HD SAMPLE SIZE

Patients would be suitable for this randomisation if they are planned for post-operative radiotherapy regardless of whether this is the early or deferred setting.

There is some uncertainty in the baseline disease-specific survival (DSS) rate for patients receiving early RT and for patients receiving deferred RT. It is assumed that patients receiving early radiotherapy do at least as well as patients receiving deferred radiotherapy, timed from randomisation to RADICALS-HD. There is also uncertainty over the proportion of early and deferred patients that would join the trial; it is assumed that at least as many patients in the deferred setting will be randomised, if not two to three times more.

Since the trial was designed in 2006, further information on the baseline estimates of disease specific survival have become available from similar patient cohorts, including data from the RTOG 9601, SWOG 8794 and EORTC 22911 trials. These provide useful estimates as they are clinical trials and recruited partly during the PSA era; such information was not previously available when RADICALS-HD was designed.

Sites and patients are encouraged to join the three-way randomisation of no-HT vs STHT vs LTHT in RADICALS-HD as this is the most efficient for the trial. However, it has become apparent that the three-way randomisation is less well supported than either of the two separate potential two-way randomisations: no-HT vs STHT and STHT vs LTHT. These are each clinically important questions and

the trial will address both. It will not be possible to address one of the originally envisaged comparisons: no-HT vs LTHT with any reasonable degree of power, although the comparison will be performed. Therefore, there are two main comparisons in RADICALS-HD:

1. RT-only (no-HT) vs RT + short-term hormone therapy (STHT)
2. RT+ short-term HT (STHT) vs RT + long-term HT (LTHT)

It is assumed that patients who enter RT+STHT vs RT+LTHT comparison have a slightly higher risk of a disease event than patients who enter RT-only vs RT+STHT comparison because the clinician assumes that some HT is required; therefore, their 10 year DSS rate is estimated as being lower.

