## **6.5 STATISTICAL ANALYSIS PLAN**

The analyses to be performed for RADICALS will be presented in detail in a separate Statistical Analysis Plan. In short, the main analyses will be performed for patients in RADICALS-RT and separately for patients in RADICALS-HD. The main outcome measures will be compared using the standard time-to-event methods of Kaplan-Meier with formal comparisons using log-rank tests and graphically represented with survival plots. Analyses in the hormone duration comparisons will be stratified by the timing of post-operative radiotherapy (early RT vs deferred RT).

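### The analysis summary does not carry the minimisation factors into the primary tests: a small, avoidable loss of power in RADICALS-HD, negligible in RADICALS-RT

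*Combined protocol and SAP*

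**What the plan says.** Section 6.1 describes allocation by "minimisation over a number of clinically important stratification factors with an allocation probability of 80" per cent and adds: "Each comparison will have an independent randomisation programme". It does not name the factors.

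Section 6.5 is a short summary that points elsewhere for detail: "The analyses to be performed for RADICALS will be presented in detail in a separate Statistical Analysis Plan". The main outcomes are to be "compared using the standard time-to-event methods of Kaplan-Meier with formal comparisons using log-rank tests". The only stratifier mentioned applies to HD: "Analyses in the hormone duration comparisons will be stratified by the timing of post-operative radiotherapy (early RT vs deferred RT"). Nothing is said about stratification or adjustment in RADICALS-RT, and no minimisation factor is said to enter any analysis.

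Section 6.3.3 defines two main HD comparisons (none vs 6 months, 6 vs 24 months) and says of the third: "It will not be possible to address one of the originally envisaged comparisons: no-HT vs LTHT with any reasonable degree of power". It adds that this comparison will still be done, without saying which men or which model it will use.

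**The concern.** Minimisation makes the arms more alike on the chosen factors than chance would. If those factors predict outcome, a log-rank test that leaves them out uses a variance that is too large for the design. The test rejects too rarely under the null, and the marginal hazard ratio lies nearer 1 than the conditional one. Precision gained at randomisation is then not used at analysis.

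This matters mainly for HD, where there is little to spare. Recruitment has closed (section 3.2), and the updated power statements in section 6.3.3 sit close to 80%. For the none vs 24 months comparison, the plan leaves both the analysis population and the use of the remaining randomised evidence open.

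**Working it through.** **Reproducing the plan's figures.** RADICALS-RT (section 6.3.2): "With 80% power, a two-sided 5% significance level, accrual lasting 5½ years", hazard ratio 0.487. Freedman: (1.960 + 0.842)² × (1.487/0.513)² = 65.9, so 66 events, as stated. HD (sections 6.3.3.A and B), Schoenfeld, power = Φ(½√events × |ln HR| − 1.96):
- 200 events at 0.67: Φ(2.832 − 1.96) = 80.8%.
- 300 events at 0.72: Φ(2.845 − 1.96) = 81.2%.

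Both agree with the stated power of over 80%, and neither formula uses strata. The margin is thin. The survival rates themselves imply ln 0.86/ln 0.80 = 0.676 and ln 0.81/ln 0.75 = 0.732, which give 79.1% and 76.9%.

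**Effect of using the factors.** Because the factors are unnamed, the following are assumptions: four binary factors, each with 40% prevalence and the same hazard ratio. Allocation was simulated by minimisation with 80% probability, and the analysis was run at the planned event count (RT n = 1063, HD n = 1480 and 1524). There were 1200-1500 runs per cell, with Monte Carlo error of about 1 point. Power is shown as unstratified / log-rank on all 16 strata / adjusted Cox:

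| Factor HR | RT, 66 events | 0 vs 6, 200 events | 6 vs 24, 300 events |
|---|---|---|---|
| 1.0 | 83.7 / 81.3 / 83.4 | 80.7 / 80.3 / 80.5 | 81.1 / 80.9 / 81.1 |
| 1.5 | 82.3 / 79.5 / 81.5 | 80.0 / 80.3 / 80.3 | 79.2 / 79.9 / 80.1 |
| 2.0 | 82.9 / 81.3 / 82.0 | 79.0 / 81.0 / 81.8 | 76.5 / 79.4 / 79.7 |
| 3.0 | 81.4 / 83.3 / 83.5 | 73.9 / 80.7 / 81.4 | 68.9 / 78.5 / 79.3 |

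Unstratified type I error at factor HR 2 and 3 was 3.2% and 3.7% for 0 vs 6, and 4.9% and 4.7% for RT. The test is conservative, not inflated.

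The HD differences are upper bounds, because the first figure uses no strata while the plan stratifies by radiotherapy timing. A closer comparator for 6 vs 24 used three factors (prevalences 20/40/60%, hazard ratios 3/2/1.7). Stratifying on any one factor gave 74-76% power and on all three 78%, a gap of 2-4 points.

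In RT, adjusted Cox moved power by between about −1 and +2 points. Full cross-stratification cost up to 2.8 points (82.3 to 79.5) when factors were weak.

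**None vs 24 months: who is in it.** Inputs are 2840 men in HD (Trial Summary), 1480 and 1524 in the two comparisons (section 6.3.3), and equal three-way allocation. A three-way 6-month man counts in both comparisons, so the overlap is 1480 + 1524 − 2840 = 164 per arm. Three-way men number 3 × 164 = 492, of whom 328 are in the direct contrast. The two-way groups are 1480 − 328 = 1152 and 1524 − 328 = 1196.

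The population needs stating because the plan expects different risk in the two comparisons. Setting all no-hormone men (80% event-free at 10 years) against all 24-month men (81%) would give ln 0.81/ln 0.80 = 0.94, while the two assumed effects multiply to 0.676 × 0.7325 = 0.50.

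**Direct power.** At the planned event fractions (200/1480 and 300/1524), 328 men yield about 44-65 events. Power is 19-36% for hazard ratios of 0.72 to 0.67, and 68-83% if the effects multiply (0.67 × 0.72 = 0.48).

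**Joint model.** Two-way events are 1152 × 200/1480 = 155.7 and 1196 × 300/1524 = 235.4. Three-way events, at an assumed 17%, are 83.6, of which 55.8 are in the direct contrast. For the log hazard ratios of 6 and 24 months against none, the information terms are:
- I₁₁ = 155.7/4 + 235.4/4 + 2(83.6)/9 = 116.4
- I₂₂ = 235.4/4 + 2(83.6)/9 = 77.4
- I₁₂ = −(235.4/4 + 83.6/9) = −68.2

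The variance for 24 months vs none is 116.4/(116.4 × 77.4 − 68.2²) = 0.0267, so the SE is 0.16. The direct SE is √(4/55.8) = 0.27. The information ratio is about 2.7. A separate simulation with 30% loss by 10 years gave 0.169 and 0.284.

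**The case against.** Section 6.5 calls itself a summary and defers to a separate analysis plan that is not among these documents. A reader might infer that the RT test is definitely unstratified, but the text is only silent. That limits the point to the analysis as described.

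The factors are called clinically important, not prognostic, and are unnamed. Every power difference above therefore rests on assumed strengths. An unadjusted hazard ratio is also a legitimate estimand, not an error, and the stated event numbers do not depend on stratification. All of this stands.

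A reader might infer that HD pools three independent programmes of differing risk. The documents do not say that. Section 6.1 gives one programme per comparison, which may simply mean RT and HD. Each main HD comparison contains at most the three-way men plus one two-way group, and the risk difference in section 6.3.3 is between comparisons. With equal allocation in each group, combining them does not bias the test. Stratifying by randomisation option is a precision measure there.

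A reader might also blame the choice of test for the weak none vs 24 months comparison, or say that question is abandoned. Neither follows. The subset is small because two-way entry was optional and better supported. The plan discloses this and will still make the comparison. Section 6.6.2 also plans a meta-analysis including RTOG 96-01, which section 1.4 describes as radiotherapy alone against radiotherapy plus two years of bicalutamide. The joint contrast is partly indirect and leans on similar effects in men whose randomisation option reflected clinical judgement, so it can only support the direct estimate.

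**Conclusion.** The point holds as an efficiency improvement, not as a validity fault. The described tests do not inflate type I error. For HD the power forgone is roughly 0-1 point at factor hazard ratio 1.5, 2-3 points at 2, and 7-10 points at 3. All three are upper bounds and depend on the assumed number, prevalence and strength of the factors. For RT the gain is negligible, and full cross-stratification with 66 events can lose 2-3 points.

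It is still worth acting on, because HD power is close to its target and the factors were already needed at randomisation.

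For none vs 24 months, restricting the direct estimate to about 328 three-way men is needed for clarity. The joint model would cut the standard error from about 0.27-0.28 to 0.16-0.17, provided hazard ratios are similar across randomisation options.

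**What to change.** In section 6.5 and the separate analysis plan:

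- Name the minimisation factors for RT and for HD.
- State that each primary analysis adjusts for them, through a covariate-adjusted Cox model or a log-rank on a few strong strata. Do not fully cross-stratify RT.
- In HD, keep radiotherapy timing and add randomisation option (three-way vs two-way) as a stratum.
- State that the direct none vs 24 months estimate uses only three-way randomised men. Beside it, as supportive, report the contrast from one Cox model of all 2840 HD men, stratified by randomisation option, with 6-month and 24-month terms and a check of consistency across options.

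The cost is wording and minor programming, with no new data. It should be settled before comparative results are seen. The drawbacks are that sparse strata need pooling or covariate adjustment, and that the joint contrast carries the similarity assumption, which the consistency check can only partly test.

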## **6.6 INDIVIDUAL PATIENT DATA META-ANALYSIS**

### **6.6.1 RADICALS-RT**

In collaboration with the two parallel trials to RADICALS-RT, RAVES and GETUG-17, and the Meta-analysis Group of the MRC-CTU at UCL, the ARTISTIC collaborative group has been formed in order to prospectively plan a meta-analysis. Pooling summary results and relevant statistics for event free survival from all three trials will facilitate a meta-analysis of almost 2000 patients in total. The resulting increase in power and precision that the meta-analysis provides will enable a timely and definitive assessment of the treatment effects of adjuvant RT in all patients as well as potentially enabling an assessment of treatment effects within subgroups of patients, defined for example by risk groups or by age at randomisation. In due course, as trial outcome data matures, the ARTISTIC collaboration will undertake a full meta-analysis based on individual participant data to assess all outcome measures (see section 1.1.4.A).

### **6.6.2 RADICALS-HD**

Other international groups are conducting overlapping clinical trials therefore, we plan to also undertake a meta-analysis using IPD including RADICALS-HD, GETUG-16, EORTC 22043/30041, RTOG 05-34 (SPPORT) and RTOG 96-01 and any other relevant trial identified in a full systematic review. Together these trials will provide increased power for analysis of both disease-specific survival and overall survival. Formal agreements will be developed with all trial groups.

## 7 QUALITY ASSURANCE AND CONTROL

### 7.1 COMPLIANCE

RADICALS will be conducted according to the protocol, relevant Standard Operating Procedures (SOPs), GCP and relevant national regulatory requirements.

### 7.2 RADIOTHERAPY QUALITY ASSURANCE

The RADICALS Radiotherapy Trials Quality Assurance (RTTQA) Group, consisting of radiation oncologists and radiotherapy physicists, will give information and guidance regarding implementation of the protocol, monitor compliance with the protocol, and provide feedback on the RTQA accreditation (where necessary).

RTQA accreditation is required by all centres (see [Appendix B](#)). However, centres that have been RTQA accredited for another multi-centre prostate radiotherapy trial in the UK (e.g. MRC RT01 or CHHIP) will be automatically granted RADICALS-RTQA accreditation.

The RADICALS website will include sample cases to illustrate the Clinical Target Volumes described in [Section 6.1.3.A](#).

Data will be collected by the NCRI Radiotherapy Trials QA (RTTQA) Group for patients treated in the RADICALS trial. This includes: CT images, contours, plan and plan dose cubes along with DVHs. Data must be appropriately anonymised.

### 7.3 MONITORING AND AUDIT

A risk assessment has been carried out and an appropriate monitoring plan has been developed. Monitoring will be a combination of central monitoring (e.g. database checks) and the IDMC review as described in [Section 15.3](#). There will be limited on-site monitoring: all participating investigators and groups must agree to direct access to all trial related sites, source data documents and reports for the purpose of monitoring by the sponsor and audit and inspection by domestic and foreign regulatory authorities.

### 7.4 SOURCE DATA

The investigator/institution should maintain adequate and accurate source documents and trial records that include all pertinent observations on each of the site's trial subjects. Source data are contained in source documents and are defined by EU guidelines as all information in original records that are used for the reconstruction and evaluation of the clinical trial. Source documents are the first place where the source data is recorded. These can include hospital records, clinical and office charts, laboratory notes, X-rays, and pharmacy dispensing records.

Source data should be attributable, legible, contemporaneous, original, accurate, and complete. Changes to source data should be traceable, should not obscure the original entry, and should be explained if necessary (e.g., via an audit trail). Each data element should only have one source.

Data will be recorded on case report forms (CRF). The original should be sent to the appropriate participating group and a copy kept at the local centre. The type of data to be recorded is detailed in Section 7, the Assessments and Procedures section.

The following data should all be verifiable from source documents, which may include paper notes and electronic health records:

- signed consent and (where applicable) assent forms
- dates of visits including dates any trial specimens were taken and processed in the laboratory
- eligibility and baseline values
- adverse events of any grade that lead to treatment modification and adverse events judged definitely/probably/possibly related to IMP
- severe (grade 3/4) adverse events
- serious adverse events
- dates IMP (hormone therapy) was dispensed and administered

#### **7.4.1 DATA HANDLING**

The site will retain a copy of each CRF. All data recorded in each CRF, will be entered onto the RADICALS trial clinical database. A comprehensive validation check program will identify missing, illogical and/or inconsistent data. Trained data management personnel will review the resulting discrepancy report, correcting any data entry errors. If investigator input is required to clarify or correct any missing, ambiguous or inconsistent data, the data manager will generate a Data Clarification Form (DCF). The Data Manager will send this form to the investigator for completion. When the completed DCF is returned to data management, the data on the clinical database will be corrected accordingly.

#### **7.5 PROTOCOL DEVIATIONS**

If the site identifies a protocol deviation they should notify the PI within 24 hours. The PI and team should review the deviation and create a suggested corrective action plan. This corrective plan should be reported to the MRC CTU team, who will review it and the deviation. The site will keep a protocol deviation log and the completed corrective action plan in order to ensure, as far as possible, that the deviation does not reoccur.

## 8 SAFETY REPORTING

ICH GCP requires that both investigators and sponsors follow specific procedures when notifying and reporting adverse events/reactions in clinical trials. These procedures are described in this section of the protocol. [Section 11.1](#) lists definitions, [Section 11.3](#) gives details of the institution/investigator responsibilities and [Section 11.4](#) provides information on MRC CTU at UCL responsibilities.

### 8.1 DEFINITIONS

The definitions of the EU Directive 2001/20/EC Article 2 based on ICH GCP apply in this trial protocol. These definitions are given in [Table 6](#). These definitions apply to RADICALS investigators in the UK and Canada.

**Table 6: Terms and definitions for adverse events**

| TERM                                                                                                                   | DEFINITION                                                                                                                                                                                                                                                                                                                                                                                                                                                      |
|------------------------------------------------------------------------------------------------------------------------|-----------------------------------------------------------------------------------------------------------------------------------------------------------------------------------------------------------------------------------------------------------------------------------------------------------------------------------------------------------------------------------------------------------------------------------------------------------------|
| Adverse Event (AE)                                                                                                     | Any untoward medical occurrence in a patient or clinical trial subject to whom a medicinal product has been administered including occurrences which are not necessarily caused by or related to that product.                                                                                                                                                                                                                                                  |
| Adverse Reaction (AR)                                                                                                  | Any untoward and unintended response to an investigational medicinal product related to any dose administered.                                                                                                                                                                                                                                                                                                                                                  |
| Unexpected Adverse Reaction (UAR)                                                                                      | An adverse reaction, the nature or severity of which is not consistent with the information about the medicinal product in question set out in the summary of product characteristics (or Investigator brochure) for that product.                                                                                                                                                                                                                              |
| Serious Adverse Event (SAE) or Serious Adverse Reaction (SAR) or Suspected Unexpected Serious Adverse Reaction (SUSAR) | Respectively any adverse event, adverse reaction or unexpected adverse reaction that: 

• results in death

• is life-threatening*

• requires hospitalisation or prolongation of existing hospitalisation**

• results in persistent or significant disability or incapacity

• consists of a congenital anomaly or birth defect

• is another important medical condition***

 |

